## 5. STUDY DESIGN

### a. STUDY TYPE & DESIGN & SCHEDULE

This study is designed as a longitudinal cohort study. The study will recruit participants for 24 months from study commencement, and each participant will be enrolled for 12 months.

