### c. STUDY METHODOLOGY

The Vaccinology and Immunology Research Trials Unit conducts surveillance of SARS-CoV-2, and influenza infections at the Women's and Children's Hospital as part of the Paediatric Active Enhanced Disease Surveillance (PAEDS) network.

Similar to current methods used by the PAEDS network, for phase 1 of the study WCHN pathology results will be searched each fortnight by a WCHN employed level 2 Registered Nurse, and SARS-CoV-2 test-positive and influenza test-positive children and adolescents (aged 0-18 years) will be invited to participate (Figure 1).

For phase 2 of the study, SARS-CoV-2, and influenza infections will be recruited from SA Health notifications of PCR or Rapid Antigen Tests (RAT), to ensure the results are generalisable to the South Australian populations and include children and adolescents with potentially milder acute illness. Once recruitment commences through SA Health notifications, this will replace invitations sent from WCHN to avoid duplication of invitations.

COVID-19 and influenza cases parents will be sent an SMS invitation, and if they consent, agree to 1) completing a baseline survey, then surveys at 3, 6, and 12 months, 2) for the research team to review EMR if they present to a SA Health hospital (WCHN, FMC, and LMH), and permission for the study team to access the Australian Immunisation Register to check COVID-19, and influenza immunisation status.

To reimburse participants for their time and encourage the completion of surveys, a \$10 online supermarket voucher will be provided upon completion of the initial, then 3, 6, and 12-month surveys for their time (\$40 in total). If parents deem that their 12-18-year-olds are mature enough to understand the relevant information and to give consent, assent will also be collected if they wish to complete the surveys themselves. If the 12-18 year old does not agree to participate from the study, they will be withdrawn from the study.

[figure not shown]

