## PARTICIPANT RECRUITMENT

### c. RECRUITMENT PROCEDURE

**Phase 1 WCH:** Each fortnight, parents of children aged 0 to 18 will be contacted if their child is identified as having a positive PCR or Rapid Antigen Test (RAT) for COVID-19 or influenza infection at the WCHN. They will be sent one phone text message informing them about the study and inviting them to participate using an online link. The link will take them to the online information sheet and consent for the study.

Before contacting the parents of WCHN hospitalised children, the electronic medical record will be checked to ensure no alerts are present.

**Phase 2 SA Health Notifications:** SA Health receive notifications of SARS-CoV-2 PCR. They also receive notification of influenza PCR-positive cases. Every month, the Disease Surveillance and Investigation Section team (CDCB) collates these notifications for COVID-19 and influenza. A list of children who have accessed the statewide WCHN palliative care service will be cross-matched with influenza and COVID-19 notifications. Influenza and COVID-19 notifications with a matching date of birth will be excluded from receiving an invitation. After data validation, an SMS will be sent to the mobile phone number of the cases. The SMS will contain a link to the information sheet and consent form, securely stored on a RedCap database housed on the CALHN server. SA Health notification data does not specify the relationship between the contact mobile number entered in the online reporting system, to the case. However, there will be wording that ensures it is clear that a parent or guardian is required to consent to the study. This recruitment method will replace invites from phase 1 (WCHN) once governance approval is provided to avoid duplication of invites.

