### 8. STATISTICAL METHODS

#### a. SAMPLE SIZE ESTIMATION & JUSTIFICATION

The study is primarily descriptive. At the Women's and Children's Hospital, in the last 12 months, October 2022 to October 2023, there have been 800 COVID-19 and 1,100 influenza-positive swabs.

SA Health notification of COVID-19 PCR tests in those under 18 has been 335 PCR positive in the last 3 months, with 600 notified by RAT. There will be variations in the numbers throughout the study due to changes in testing and new variants. One possible change will be that RAT results will no longer be collected. Estimated invites to be sent to SA Health notified cases are 1,340 from PCR results and 2,400 from RAT results. Year to date 9,343 influenza cases under the age of 18 have been reported (with 8,270 notified between April and October 2023)

Assuming 15% participation, based on response rates from similar studies, there would be approximately 1,222 COVID-19 cases, with 2,800 non-COVID-19 cases from SA Health notification over the 24 months of the study.

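### The 2,800 influenza projection credits statewide notifications for all 24 recruitment months, although a hospital-only Phase 1 of unstated length lies inside them

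*Protocol*

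**What the plan says.** Section 5.a sets the recruitment window: "The study will recruit participants for 24 months from study commencement, and each participant will be enrolled for 12 months".

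Section 5.c splits that window into two phases. Phase 1 invites children with positive results in the WCHN pathology system. Phase 2 uses SA Health notifications. The phases run one after the other: "Once recruitment commences through SA Health notifications, this will replace invitations sent from WCHN to avoid duplication of invitations". Section 6.c ties the switch to an undated event: "This recruitment method will replace invites from phase 1 (WCHN) once governance approval is provided to avoid duplication of invites". No length is given for Phase 1.

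Section 8.a gives yearly hospital counts (800 COVID-19 and 1,100 influenza swabs), statewide COVID-19 counts ("335 PCR positive in the last 3 months, with 600 notified by RAT"), the resulting invitations ("Estimated invites to be sent to SA Health notified cases are 1,340 from PCR results and 2,400 from RAT results") and a year-to-date count of 9,343 influenza notifications, 8,270 of them from April to October 2023. The participation rate is borrowed from comparable work ("Assuming 15% participation, based on response rates from similar studies"). The COVID-19 cohort is put at roughly 1,222, and the influenza cohort is described in these terms: "with 2,800 non-COVID-19 cases from SA Health notification over the 24 months of the study". The synopsis repeats these totals. Section 8.b then bases its precision range of 0.62% to 1.47% on 1,222 COVID-19 cases with 20% loss.

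**The concern.** The influenza total is attributed to a recruitment stream that the design does not run for the whole window. The hospital counts that would apply in Phase 1 are listed in Section 8.a but do not enter that total. They are far smaller than the statewide counts: 1,100 / 9,343 = 12% for influenza and 800 / 3,740 = 21% for COVID-19.

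The influenza cohort is the comparator for secondary objective 2 and the whole sample for secondary objectives 1, 7 and 10. The COVID-19 number carries the precision statement in Section 8.b, and a hospital-only period lowers that number as well.

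**Working it through.** **Inputs (Section 8.a unless noted).** Participation 15%. SA Health influenza 9,343, first taken as one year. SA Health COVID-19 invitations 1,340 + 2,400 = 3,740, which is four times the three-month counts (4 x 335 and 4 x 600), so one year. WCHN 1,100 influenza and 800 COVID-19 a year. Recruitment 24 months (Section 5.a). Loss 20% and population 360,000 (Section 8.b). Phase 1 length m is not stated and is therefore an assumption.

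**1. Reproducing the stated totals.**
- Influenza: 9,343 x 2 x 0.15 = 2,802.9. This reproduces 2,800, with no allowance for hospital-only months.
- COVID-19: 3,740 x 2 x 0.15 = 1,122. This does not reproduce 1,222. The gap of 100 is a separate discrepancy and is present even with m = 0.

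**2. Monthly yield at 15%.**
- Influenza: SA Health 9,343 x 0.15 / 12 = 116.8; WCHN 1,100 x 0.15 / 12 = 13.75; difference about 103.
- COVID-19: SA Health 3,740 x 0.15 / 12 = 46.75; WCHN 800 x 0.15 / 12 = 10.0; difference about 37.

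**3. Totals by Phase 1 length, flat rates.** Influenza = 13.75m + 116.8(24 - m). COVID-19 = 10m + 46.75(24 - m). The margin is 1.96 x sqrt(p(1 - p)/n) with n = 0.8 x the COVID-19 total and the finite-population correction for 360,000. This formula reproduces all nine cells of Table 2, so the table's figures are half-widths.

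| m (months) | Influenza | COVID-19 | COVID-19 after 20% loss | Margin at 1% | Margin at 6% |
|---|---|---|---|---|---|
| 0 | 2,803 | 1,122 | 898 | 0.65 | 1.55 |
| 3 | 2,494 | 1,012 | 809 | 0.68 | 1.63 |
| 6 | 2,185 | 902 | 721 | 0.73 | 1.73 |
| 12 | 1,566 | 681 | 545 | 0.83 | 1.99 |

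Against 2,800, the influenza totals at 3, 6 and 12 months are lower by 11%, 22% and 44%. Part of the widening in the COVID-19 margins (0.65 to 1.55 already at m = 0) comes from the separate 1,222 discrepancy.

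**4. Sensitivity of the influenza figure.**
- *Phase 1 covers one April to October season.* 2,803 - 8,270 x 0.15 + 1,100 x (8,270 / 9,343) x 0.15 = 2,803 - 1,240.5 + 146 = about 1,708, or 39% below 2,800.
- *9,343 covers only ten months (assumption), with two months added at the January to March rate.* (9,343 - 8,270) / 3 = 358 a month. The year is then 9,343 + 2 x 358 = about 10,058, and 24 months give about 3,018. A four-month off-season Phase 1 leaves 3,018 - 4 x 358 x 0.15 = about 2,803 before any hospital recruits. Losing a season leaves about 3,018 - 1,240.5 + 146 = 1,923, or 31% below 2,800.
- *9,343 annualised flat from ten months.* 9,343 x 1.2 x 2 x 0.15 = about 3,363. Each Phase 1 month then costs 0.15 x (934.3 - 91.7) = 126.4, so 2,800 survives (3,363 - 2,800) / 126.4 = about 4.5 months. Twelve months leave about 1,847.

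**The case against.** A reader might infer that the stated cohort sizes hold only if Phase 1 has zero length. The documents do not support that for either virus. The 1,222 does not follow from the stated invitations even with no Phase 1, so Phase 1 is not what breaks it. For influenza, 9,343 is a year-to-date count and cases cluster in April to October, so 2,800 could survive a short off-season Phase 1. The eligibility look-back (three months in Section 6.a, two in the synopsis) might also recover some notifications at the switch. These points stand and limit the claim.

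It can also be said that the study is mainly descriptive, that the totals are labelled approximate, that Section 8.a warns of changing testing and variants, and that no power claim, precision claim or enrolment target rests on 2,800. Even a 12-month Phase 1 leaves about 1,566 influenza participants. Table 2 shows margins down to a sample of 550, close to the 545 that a 12-month Phase 1 leaves. This keeps the matter modest. It does not remove it: the protocol itself describes a change of recruitment source, which is not the random variation the caveats address, and the other rows of Table 2 do not correct the sentence in Section 8.b that is tied to 1,222.

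Finally, the size of the effect depends on a Phase 1 length that nobody has written down. That is true, and it is part of the finding.

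**Conclusion.** The point holds in a limited form. The influenza projection assumes notification-based recruitment for all 24 months, while the same protocol places a hospital-only phase of unstated length within them. The expected cost is about 103 influenza and 37 COVID-19 participants per Phase 1 month, assuming 15% participation in both phases, flat accrual and 9,343 as a full year.

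The direction of the COVID-19 effect is certain, because the hospital yield is about a fifth of the statewide yield. The influenza effect ranges from negligible (short, off-season, annualised count) to a loss of roughly 30% to 45% (a full season or a full year in Phase 1). The precision range in Section 8.b is somewhat optimistic: 0.73 to 1.73 points for six months of Phase 1 and 0.83 to 1.99 for twelve, against 0.62 to 1.47. The validity of the planned estimates is not in question, only the numbers and margins that the protocol states for them.

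**What to change.** In Section 8.a and in the synopsis entry for planned subjects:

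- State the actual or expected length of Phase 1 and the months it covers.
- Compute the planned numbers by phase: WCHN swabs x 15% for the Phase 1 months, plus SA Health notifications x 15% for the rest of the 24.
- Put 9,343 on a 12-month basis and count influenza by the seasons that fall in each phase.
- Restate both totals. For COVID-19, start from the 3,740 yearly invitations, and correct or explain the 1,222 at the same time.

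In Section 8.b, restate the precision range at the resulting COVID-19 number after 20% loss.

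The cost is a recalculation and a few changed sentences, with no additional enrolment. The downside is smaller stated cohorts and a slightly wider stated margin.

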#### b. POWER CALCULATIONS

If the long-COVID incidence is between 1% to 6%, a sample size of 1,222 COVID cases allows for the incidence to be estimated with a precision ranging from 0.62% to 1.47%, with 20% loss to follow-up over 12 months (with precision defined as the width of a 95% CI around the estimated incidence).

**Table 2 Precision estimates based on either the proportion of long COVID in the population (between 1-6%) and the sample size ( between 550-2000)**

|             | Proportion with long COVID             |       |       |
|-------------|----------------------------------------|-------|-------|
|             | 1%                                     | 3%    | 6%    |
| Sample size | Margin of error for incidence estimate |       |       |
| 550         | 0.83%                                  | 1.42% | 1.98% |
| 1,000       | 0.62%                                  | 1.06% | 1.47% |
| 2,000       | 0.43%                                  | 0.75% | 1.04% |

Assume 360,000 population at risk (children under 18 in South Australia)

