By the end of 2022, approximately 450,000 children under 9 and 575,000 adolescents aged 10-19 in Australia had confirmed COVID-19 infections. Using 1.2% to 16% as a guide, this translates to around 12,300 to 166,000 Australian children experiencing post-acute sequelae lasting 3 months or longer, which does not account for repeat infections. However, in Australia, the combination of high vaccination rates and the Omicron variant predominance amongst total primary infections suggest that the incidence of long COVID might differ from that in other countries. Even with a lower proportion of PCC in children and adolescents, the absolute number of infections indicates a need for a more coordinated and informed approach to managing PCC in Australian children and adolescents. The authors of the SCHN study highlight the need to develop pathways to support screening of children for long COVID and provide better guidance for primary care services. They also point out that there is currently no comprehensive approach to collect data on PCC across the lifespan, which is required to inform management of the condition and implementation of interventional studies. While there is currently no known effective treatment, COVID-19 vaccination has demonstrated some protection in adults and children aged 5-17, (effectiveness of 41.7% (15.0 - 60.0) against diagnosed long COVID), although it is less effective in younger age groups, and not effective at 18 months since the last vaccination. Many pharmaceutical candidates are undergoing trials to establish if they are an effective therapeutic intervention.

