### c. STATISTICAL METHODS TO BE UNDERTAKEN

Analyses will follow a pre-specified statistical analysis plan. The cumulative incidence of PCC following COVID-19 (primary objective) and PAS following influenza will be estimated at 3 months post-infection, with 95% confidence intervals. The proportion of individuals with ongoing symptoms will be reported descriptively (n, %) at 6 and 12 months. The relative risk of developing PCC following COVID-19 versus developing PAS following influenza (objective 2) will be estimated using a log-binomial model. A multivariable logistic model will be developed for predicting PCC at 3 months (objective 3), incorporating pre-specified predictors such as age (treated as continuous), sex, pre-existing conditions, and socioeconomic status. Model performance will be evaluated using the area under the receiver operating characteristic curve, with internal validation by bootstrap resampling in line with TRIPOD recommendations. The relatively small expected number of PCC events may limit the number of predictors that can be incorporated into the final model and hence its predictive accuracy. Linear and negative binomial mixed-effects models will assess differences between comparator groups over time in continuous (PedsQL quality of life and fatigue scores, objectives 4 and 5) and count (days absent, objective 6) outcomes, respectively. Log binomial models will compare the risk of developing PAS according to influenza vaccine uptake (objective 7) and the risk of PCC by COVID-19 reinfection (objective 8). The duration and clinical features of PCC and PAS will be described using summary statistics, with summaries at 3, 6 and 12 months. Descriptive analyses will be based on complete case data.

Handling of follow-up and missing data.

Outcomes will be summarised at the planned 3, 6 and 12-month assessments. Participants contribute data to each analysis for which follow-up information is available. For the primary objective, participants with PCC at 3 months who discontinue or miss assessments at 6 or 12 months will be treated as missing for whether symptoms were ongoing at these time-points. Multiple imputation may be considered for the prediction model, depending on the amount and reasons for missing data at 3 months when determining PCC.

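### The 95% precision of 0.62 points stated for 1% incidence rests on about 10 events and delivers about 92% coverage; the same sentence calls half-widths the width of the interval

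*Protocol*

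**What the plan says.** Section 8.b of the protocol makes a conditional statement. It opens "If the long-COVID incidence is between 1% to 6" per cent and continues that "a sample size of 1,222 COVID cases allows for the incidence to be estimated with a precision ranging from 0.62% to 1.47" per cent, "with 20% loss to follow-up over 12 months". It adds in brackets "with precision defined as the width of a 95% CI around the estimated incidence".

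Table 2, in the same section, gives nine figures for 550, 1,000 and 2,000 children at 1%, 3% and 6%, under the label "Margin of error for incidence estimate". The two figures in the sentence are the ends of the 1,000 row. A note under the table reads "Assume 360,000 population at risk (children under 18 in South Australia").

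Section 8.c says that the primary incidence "will be estimated at 3 months post-infection, with 95% confidence intervals". It names no interval method.

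**The concern.** The normal approximation is weak when few events are expected, and the 1% column of Table 2 expects only 5.5 events at 550 children and 10 at 1,000. A symmetric interval there tends to sit too low and to be too short on its upper side. The plan would then present as 95% precision something that falls short of it, with the shortfall on the side where burden is underestimated. Separately, the sentence and the table give different names to the same numbers, and the two names differ by a factor of two.

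**Working it through.** **Inputs.** All are from section 8.b: 1,222 COVID-19 cases, 20% loss, incidence 1% to 6%, 95% confidence, population 360,000. Evaluable children: 1,222 x 0.8 = 977.6, taken as 978. Expected events: 978 x 0.01 = 9.8 and 978 x 0.06 = 58.7.

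**Reproducing the plan's figures.** The half-width is 1.96 x sqrt(p(1-p)/n), multiplied by sqrt((360,000-n)/359,999). All nine cells of Table 2 reproduce to rounding. Examples:
- n = 1,000, 1%: 1.96 x sqrt(0.01 x 0.99/1,000) = 0.617 points, or 0.616 with the factor. Stated: 0.62.
- n = 1,000, 6%: 1.472 points, or 1.470 with the factor. Stated: 1.47.
- n = 978: 0.62 points at 1% and 1.49 at 6%.

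So the figures are correctly calculated as half-widths. The full widths at n = 978 are 2 x 0.624 = 1.25 points and 2 x 1.488 = 2.98 points.

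**Coverage of the symmetric interval.** For each possible event count x, form the interval x/n ± 1.96 x sqrt((x/n)(1-x/n)/n), check whether it contains the true p, and sum the binomial probabilities.

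| n | True incidence | Expected events | Coverage | Upper limit below truth |
|---|---|---|---|---|
| 550 | 1% | 5.5 | 90.8% | 8.7% |
| 978 | 1% | 9.8 | 92.0% | 7.5% |
| 1,000 | 1% | 10 | 92.7% | 6.6% |
| 2,000 | 1% | 20 | 94.9% | 3.8% |
| 978 | 6% | 58.7 | 94.7% | 3.4% |

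The 7.5% can be seen directly. With 5 events in 978 the upper limit is 0.96%, below 1%, and the probability of 5 or fewer events at a true 1% is 7.5%.

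This is not an accident of choosing exactly 1%. At n = 978, over true incidence from 0.8% to 1.2%, coverage averages 92.5% and ranges from 88.9% to 95.0%. Nor does it depend on the loss assumption: with all 1,222 children, coverage at 1% is 91.4%.

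**Wilson limits.** The limits are [p̂ + z²/(2n) ± z x sqrt(p̂(1-p̂)/n + z²/(4n²))] / (1 + z²/n). For 10 events in 978 (1.02%) they are 0.56% to 1.87%, and the exact Clopper-Pearson limits are 0.49% to 1.87%. Averaging the Wilson margins over the binomial distribution at n = 978:
- 1%: +0.84/-0.45 points, mean half-width 0.64, coverage 94.8%.
- 6%: +1.66/-1.32 points, mean half-width 1.49, coverage 95.0%.

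The mean exact half-width at 1% is 0.68 points. The upper margin at 1% is therefore 0.84/0.62 = 1.35 times the stated figure, although the total width changes little.

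**The case against.** A symmetric normal margin is a routine planning figure, and at 1% the mean half-width rises only from 0.62 to 0.64 points (Wilson) or 0.68 (exact). That is true, and it keeps the point small. It does not remove it: the half-width averages out an asymmetry of +0.84 against -0.45, and the coverage shortfall is real.

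Four stronger readings are tempting, and the protocol does not support them.
- **That the precision fails at both ends.** The statement is conditional on 1% to 6%, and at 6% it holds. Within the 1% column, the cell for 2,000 children is also sound.
- **That 1.47 points is wrong because the background section runs to 16%.** Section 3.c does say "Using 1.2% to 16% as a guide", but it does so to scale national burden, and the upper value is a pooled international figure. The same section says that incidence in Australia might differ. The Sydney cohort described there gives 1.2% to 6.1%, with 3.0% unable to resume usual activities and 63/1,731 = 3.6% judged to have a post-COVID condition. Those figures support the planned range, although 8.b does not say so. At 16% the margin would be about 2.3 points; the protocol makes no claim there.
- **That reported results will understate burden.** This assumes a symmetric interval in the analysis. Section 8.c commits to none, and the choice can properly be left to the statistical analysis plan.
- **That the study's size depends on these figures.** Section 8.a derives 1,222 from expected notifications and 15% participation; precision follows from that number.

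The 360,000 population factor changes the margins by at most about 0.003 points and is not at issue.

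**Conclusion.** The point holds for the low end of the stated range. At 1% incidence and 978 evaluable children, the figure given as 95% precision corresponds to about 92% coverage, with the upper limit too low in 7.5% of samples. At 550 children coverage is about 91%. At 6% the figure is adequate. The description of these half-widths as the width of the interval is a plain wording error, by a factor of two on the protocol's own definition.

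This assumes simple binomial sampling and the protocol's 20% loss applied in full to the 3-month estimate. The consequence is modest: the planning statement is somewhat too favourable at low incidence, and neither the design nor the number of participants is affected.

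**What to change.** In section 8.b, recompute Table 2 and the sentence above it with Wilson or exact limits, and show lower and upper margins separately. With Wilson limits averaged as above, the table would read, in percentage points:

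| n | 1% | 3% | 6% |
|---|---|---|---|
| 550 | +1.22/-0.54 | +1.77/-1.12 | +2.30/-1.69 |
| 1,000 | +0.82/-0.45 | +1.25/-0.89 | +1.64/-1.31 |
| 2,000 | +0.54/-0.35 | +0.84/-0.66 | +1.13/-0.96 |

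For the sentence itself, at 978 children, the range runs from about +0.84/-0.45 points at 1% to about +1.66/-1.32 at 6%. In the same edit, replace the definition of precision as the width of the interval with one that matches the margins shown.

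Optional: one sentence justifying the 6% ceiling from the local figures in section 3.c, or a further column (about ±2.3 points at 16%). There is no need to name the interval method in 8.c or to remove the 360,000 factor.

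The cost is a text and table edit and a slightly less favourable stated precision at low incidence. No extra participants are needed.

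### Section 8.b defines its precision of 0.62% to 1.47% as the width of the 95% CI, but these figures are half-widths, so the sentence claims an interval half as wide as the design gives

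*Protocol*

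**What the plan says.** Section 8.b (Power Calculations) takes an incidence of 1% to 6% and states that "a sample size of 1,222 COVID cases allows for the incidence to be estimated with a precision ranging from 0.62% to 1.47"%. The same sentence says that this already allows for attrition, put at one fifth of participants over the year of follow-up. A parenthesis then fixes the meaning of the term: "with precision defined as the width of a 95% CI around the estimated incidence".

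Table 2, directly below, gives a grid of three sample sizes (550, 1,000 and 2,000) by three incidences (1%, 3% and 6%). Its column heading is "Margin of error for incidence estimate". The two figures in the sentence are the outer cells of the 1,000 row: "1,000 | 0.62% | 1.06% | 1.47"%. A note under the table reads "Assume 360,000 population at risk (children under 18 in South Australia").

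Section 8.a calls the study primarily descriptive. Sections 4.c and 8.c place the primary estimate, the cumulative incidence of PCC, at 3 months with a 95% confidence interval.

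**The concern.** The same two numbers carry two meanings a few lines apart: a full width in the text and a margin of error in the table. These differ by a factor of two, so only one can be right. Loose use of the word precision cannot explain it, because the sentence defines the term.

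The primary objective is an estimate with an interval, not a test, so the stated precision is what tells an ethics committee, funder or reader how informative the result will be. Taken literally, the sentence promises roughly 0.69% to 1.31% at a true incidence of 1% (1 ± 0.31) and 5.27% to 6.74% at 6% (6 ± 0.735). If the table's label is right, the intervals are about 0.38% to 1.62% and 4.53% to 7.47%.

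**Working it through.** **Inputs, all from section 8.b.** Two-sided 95% level (z = 1.96); incidence p of 1%, 3% and 6%; 1,222 cases; 20% loss over 12 months; population N = 360,000.

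**Step 1: reproduce the plan's figures.** Half-width h = z × √(p(1−p)/n), multiplied by the finite population correction √((N−n)/(N−1)).

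At n = 1,000:
- p = 1%: 1.96 × √(0.0099/1,000) = 0.617 points; with the correction, 0.616. Stated: 0.62.
- p = 3%: 1.057; with the correction, 1.056. Stated: 1.06.
- p = 6%: 1.96 × √(0.0564/1,000) = 1.472; with the correction, 1.470. Stated: 1.47.

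The other two rows, with the correction, also match the printed values:

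| n | 1% | 3% | 6% |
|---|---|---|---|
| 550, computed / printed | 0.83 / 0.83 | 1.42 / 1.42 | 1.98 / 1.98 |
| 2,000, computed / printed | 0.43 / 0.43 | 0.75 / 0.75 | 1.04 / 1.04 |

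All nine cells are therefore half-widths, and Table 2 is labelled correctly.

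**Step 2: can the figures be full widths?** Full width = 2h, shown here without the correction, whose factor is about 0.999 at these sizes.

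| Evaluable n | Half-width, 1% to 6% | Full width, 1% to 6% |
|---|---|---|
| 1,000 (row quoted) | 0.62 to 1.47 | 1.23 to 2.94 |
| 978 (1,222 × 0.8 = 977.6) | 0.62 to 1.49 | 1.25 to 2.98 |
| 1,222 (no loss) | 0.56 to 1.33 | 1.12 to 2.66 |

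No row gives a full width near 0.62 to 1.47. Exact (Clopper–Pearson) limits do not help: with 10 and 59 events among 978, the full widths are 1.38 and 3.09 points.

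**Step 3: what the sentence would need if taken literally.** Solving 2h = w for n, without the correction, gives n = p(1−p) × (2 × 1.96/w)².
- p = 1%, w = 0.62 points: 0.0099 × (3.92/0.0062)² ≈ 3,960.
- p = 6%, w = 1.47 points: 0.0564 × (3.92/0.0147)² ≈ 4,010.

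That is about four times the 978 evaluable children in the plan.

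**The case against.** The strongest reply is that nothing has been miscalculated. One word in a parenthesis is wrong, the correct label stands in the table just below, and a careful reader will recover the meaning. No target width is set, and the expected number comes from notification counts and a 15% participation assumption, so no design decision rests on the word. All of this stands, and it is why the point is a correction of wording rather than a challenge to the design. It does not make the sentence true.

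Four stronger readings are tempting, and the documents do not support them.

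- *The study is too small.* The figure of about 4,000 shows only what the sentence would imply if read literally. With no required width in the protocol, there is no target for the planned sample to miss.
- *The primary objective has no valid planning statement.* It has one: Table 2 is correct and covers 550 to 2,000 participants.
- *Quoting the 1,000 row instead of 978 is a further error.* The lower half-width stays at 0.62 and the upper moves from 1.47 to 1.49, which is immaterial.
- *The range should be restated for a case count other than 1,222.* Whether 1,222 follows from the section 8.a inputs is a separate question. That section also reports hospital swabs, and phase 1 recruits from the hospital, so the matter is not settled here.

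The choice of interval method, such as exact or Wilson limits at the 1% end, is commonly left to the statistical analysis plan and is not part of this point.

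**Conclusion.** The point holds as an internal contradiction. The 0.62% and 1.47% in section 8.b are 95% half-widths at n = 1,000, and the sentence wrongly defines them as the width of the interval. As worded, it claims an interval half as wide as the design gives.

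The conclusion rests on the protocol's incidence range and case count and on the usual normal approximation, which reproduces its table. One uncertainty remains about the denominator. The 20% loss is stated over 12 months, the primary estimate is at 3 months, and no 3-month loss is given. If loss by 3 months lies between none and the full 20%, the full width lies between 1.12 and 1.25 points at 1% incidence and between 2.66 and 2.98 points at 6%. The factor of two is the same throughout.

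Severity: should fix. The sample size, the table and the analysis are unaffected.

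**What to change.** In section 8.b, replace *width* with *half-width (margin of error)* so that the text agrees with Table 2, and state the range for the protocol's own evaluable number. For example: *with 1,222 cases enrolled and 20% lost to follow-up (978 evaluable), the half-width (margin of error) of the 95% CI would be 0.62 to 1.49 percentage points for an incidence of 1% to 6%, a full width of about 1.25 to 2.98 points.* It would help to add that the full widths would be about 1.12 to 2.66 points if none of the 1,222 were lost by the 3-month primary assessment.

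If the expected number of COVID-19 cases is revised for other reasons, recompute the range from the same formula.

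The cost is one sentence. No change to recruitment, sample size, data collection or analysis is needed. The only consequence is that the stated precision looks less favourable than a literal reading now suggests.
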